##### Clinical outcomes

Patient-reported outcomes, which includes the Oswestry Disability Index (ODI) score for lumbar disabilities, EuroQol-5-dimensions-5-level (EQ-5D-5L) value for overall quality of life, and VAS pain scores, will be collected before surgery and AT 12, 24, and 52 weeks postoperatively. Safety will be assessed by evaluating adverse events and effects which is related to surgery. Adverse events and surgery-related effects will be made report to the appropriate institution. Laboratory tests for the rhBMP-2 antibody will be performed before surgery and at 12 weeks after surgery. These results and data will be compiled by a blinded assessor and enrolled using the eCRF system (Table 2).

**Table 2 Tab2:** Evaluation schedule

Visit type	Screening	Operation	Follow-up		
Visit	1	2	3	4	5
Visit week	− 4 ~ 0 weeks	0 ~ 2 days	12 weeks	24 weeks	52 weeks
			± 5 weeks	± 8 weeks	± 8 weeks
Trial description and consent	○				
Demographic data^a^	○				
Physical examination	○				
Vital sign	○				
Laboratory test^b^	○				
Bone mineral density	○				
Sampling for rhBMP-2 antibodies^c^	○		○		
Inclusion/Exclusion criteria	○	○			
Randomization		○			
Operation		○			
Simple radiographs	○				
Computed tomography					○
ODI	○		○	○	○
EuroQol-5-dimensions	○		○	○	○
VAS	○		○	○	○
Union rate evaluation^d^					○
Concomitant drug		○	○	○	○
Adverse events		○	○	○	○

*rhBMP-2* recombinant human bone morphogenetic protein-2; *ODI* Oswestry Disability Index; and *VAS* visual analog scale

^a^Baseline patient characteristic, including past medical/surgical history, physical examination

^b^including CBC, chemistry, urinalysis, urine HCG test

^c^Test for BMP-2 antibody baseline. Applicable only to the rhBMP-2 control group after surgery

^d^Evaluation in simple radiographs and CT by 2 independent orthopedic specialists who do not participate in this study process

### Sample size

This clinical study will compare the interbody fusion rate between the two groups at 52 weeks after surgery and determine whether *E. coli*-derived rhBMP-2 with HA is non-inferior to auto-iliac bone graft in TLIF. According to a previous report, the interbody bone union rate was 92.7% on CT at 12 months postoperatively [14]. For the primary outcome analysis, we calculated that a sample size of 154 participants would provide at least 90% power to show the non-inferiority of rhBMP-2 with HA graft to autogenous iliac bone graft with a one-sided alpha value of 0.05 and a non-inferiority margin of 10% for the 12-month fusion rate of TLIF with the PEEK cage, assuming a 15% dropout rate at 12 months. The sample size was calculated by Power Analysis and Sample Size software, version 15 (NCSS, Kaysville, UT, USA). Therefore, this trial will recruit 154 participants to confirm the equivalence between the rhBMP-2 active group and auto-iliac bone graft control group in TLIF.

### Safety reporting

Safety will be assessed by evaluating all adverse events and effects which is related to surgery. If unexpected severe side effect occurs during the study, the researcher will report them to the IRB of the hospital and research staff as soon as possible and follow up continuously until the complications disappear or stabilize.

### Statistical analysis

Modified intention-to-treat (mITT) and per-protocol (PP) analyses will be conducted. The primary outcome will be analyzed using the PP strategy. The interbody fusion rate at 12 months after surgery in the rhBMP-2 group will be considered non-inferior to that in the auto-iliac graft group if the lower limit of the 95% confidence section of the fusion rate in the rhBMP-2 group is limited to within the non-inferiority margin of 10%. The mITT strategy will be the principle analysis for secondary outcomes, and we will analyze whether participants received a randomized graft material to reduce the effects of crossover and drop out that could disable the randomization of both groups assigned.

To evaluate the randomized graft material effect on clinical outcomes (i.e., ODI, EQ-5D-5L, and VAS pain scores), a linear repeated-measures mixture model is going to be used. Other radiographic and clinical outcomes and side effects between the two groups will be analyzed used by the chi-square test for categorical variables and the Student’s t test for continuous variables.

All statistical analyses will be performed using Stata/MP 17.0 (StataCorp LLC, College Station, TX). Statistical significance will be defined as a two-sided *p* value < 0.05, except for the *p* value from the non-inferiority test, which was one-sided.

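### The only written non-inferiority criterion puts the 95% limit on the rhBMP-2 group's own fusion rate, not on the difference between the randomised groups

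*Protocol article*

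**What the plan says.** The success criterion for the primary outcome stands in the protocol article under Statistical analysis. rhBMP-2 counts as non-inferior under this condition: "lower limit of the 95% confidence section of the fusion rate in the rhBMP-2 group is limited to within the non-inferiority margin of 10" (percent). The same section describes significance testing as two-sided, "except for the *p* value from the non-inferiority test, which was one-sided".

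The Sample size section describes a comparison of two arms: "This clinical study will compare the interbody fusion rate between the two groups at 52 weeks after surgery". It gives "a one-sided alpha value of 0.05", "a non-inferiority margin of 10% for the 12-month fusion rate of TLIF with the PEEK cage" and one planning rate: "the interbody bone union rate was 92.7% on CT at 12 months postoperatively". It claims that "a sample size of 154 participants would provide at least 90% power", allowing for 15% dropout.

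No other part of the article states a criterion on the between-group difference.

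**The concern.** A non-inferiority margin between randomised arms is a limit on the difference between them. The interval tested against it must carry the sampling error of both arms. The written criterion builds the interval from one arm only, and it does not say what the limit is compared with, whether it is one- or two-sided, or how it is calculated.

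This sentence decides the trial's primary, confirmatory conclusion. If it is applied literally, the control arm's uncertainty drops out, or in one reading the control arm drops out altogether. If it is not applied literally, the comparator and the level are left to be chosen at analysis, possibly after the data have been seen.

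**Working it through.** **Inputs.** 77 per arm (Abstract), 15% dropout, planning rate 92.7%, margin 10% read as 10 percentage points, one-sided alpha 0.05 (all Sample size). Evaluable per arm: 77 × 0.85 = 65.45, taken as 65. At the non-inferiority boundary the true rates are 92.7% for control and 82.7% for rhBMP-2.

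**The plan's own figure.** Only one fusion rate is given, so take it for both arms:
- n = (1.645 + 1.282)² × 2 × 0.927 × 0.073 / 0.10² = 115.9, so 116 evaluable per arm.
- 116 / 0.85 = 136.5, so 137 per arm and 274 in total. The stated 154 is not reproduced.
- 154 does result from rates that the Sample size section does not state, for example 95% for rhBMP-2 v 92.5% for control: 8.564 × (0.0475 + 0.0694) / 0.125² = 64.1, so 65 per arm; 65 / 0.85 = 76.5, so 77 per arm.

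That is a separate matter. Here it matters only because 65 per arm is the size at which the criterion will be applied.

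**Possible completions of the sentence.** The article supplies none of them.

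*1. Limit compared with the observed control rate minus 10 points.* The rule passes if p̂_T − z·SE_T > p̂_C − 0.10. At the boundary, p̂_T − p̂_C + 0.10 has mean zero and standard error SE_diff, so in large samples the false-positive rate is 1 − Φ(z·SE_T / SE_diff).
- SE_T = √(0.827 × 0.173 / 65) = 0.0469.
- SE_diff = √(0.827 × 0.173 / 65 + 0.927 × 0.073 / 65) = 0.0569.
- z = 1.96: 1 − Φ(1.615) = 5.3%. z = 1.645: 1 − Φ(1.355) = 8.8%.

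Exact enumeration over both binomial arms, 65 each:

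| Limit on the rhBMP-2 rate | Nominal | Wald | Wilson | Clopper-Pearson |
|---|---|---|---|---|
| Two-sided 95% | 2.5% | 8.4% | 4.1% | 3.6% |
| One-sided 95% | 5% | 11.6% | 7.6% | 6.0% |

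*2. Limit compared with a fixed 82.7% (92.7% − 10).* With a two-sided 95% limit, the error when rhBMP-2 is truly 10 points worse depends on the true control rate:
- control 85%: 0.03-0.1%
- control 92.7%: 2.2% (Wilson, Clopper-Pearson) to 5.2% (Wald)
- control 97%: 13.5-24.3%

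*3. Limit within 10 points of the group's own estimate.* This tests precision only. The Wald half-width with 65 patients is 6.3 points at 92.7% and 9.2 points at 82.7%, so the rule is met at both rates.

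**Rule on the difference, for comparison.** Pass if the lower limit of p_T − p_C lies above −10 points; same boundary, 65 per arm, exact enumeration:

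| Limit on the difference | Nominal | Newcombe | Wald |
|---|---|---|---|
| Two-sided 95% | 2.5% | 2.5% | 3.3% |
| One-sided 95% | 5% | 4.9% | 6.0% |

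**A case where the verdict changes.** Suppose 59/65 (90.8%) fuse on rhBMP-2 and 60/65 (92.3%) on control.
- Completion 1, two-sided 95% Wald limit: 83.7% against 82.3%, a pass.
- Completion 1, Wilson limit: 81.3% against 82.3%, a fail.
- Difference, two-sided 95% Wald limit: −11.1 points, a fail.
- Difference, one-sided 95% Wald limit: −9.6 points, a pass.

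The verdict on the same data turns on choices that the sentence leaves open.

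**The case against.** The best defence is that this is loose English. The same sentence opens by calling the rhBMP-2 rate non-inferior to the rate in the auto-iliac group. The Sample size section says that the study will "compare the interbody fusion rate between the two groups at 52 weeks after surgery". The Discussion says that the primary outcome will be compared with auto-iliac graft. A limit on one arm's rate cannot lie within a margin without a reference, so the likeliest explanation is that a reference to the difference was dropped. Most of this stands, and it makes a deliberate single-arm method unlikely. It does not put a criterion on the difference into the document, and a later analysis on the difference would depart from the only criterion published.

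It is also fair to say that the error rates belong to completions supplied by the reader. A reader might infer that the rule definitely breaches the trial's type I error. The documents do not support that. They fix neither comparator, method nor sidedness, and the design alpha is one-sided 5%. Against that 5%, the two-sided Wilson and Clopper-Pearson figures (4.1% and 3.6%) are below it, the large-sample 5.3% is about equal to it, and only Wald (8.4%) clearly exceeds it.

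A reader might also infer that the control arm plays no part in the verdict, with errors of 14-24%. That needs a fixed 82.7% threshold, which the article never states, and a true control rate of 97% rather than the planned 92.7%.

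Finally, the interval method could be left to an analysis plan that is not shown. That is true of the method. It is not true of the quantity the interval is for, which this sentence states, and states wrongly.

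**Conclusion.** The point holds as a defect in the written decision rule. The sole stated criterion is for one arm's rate, lacks a reference value, and does not match the two-arm comparison for which the margin and alpha were set.

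Its numerical consequence is conditional. Against the observed control rate minus 10 points, false non-inferiority is 3.6-8.4% for a two-sided 95% limit and 6.0-11.6% for a one-sided 95% limit. The one-sided version exceeds its nominal 5% with all three interval methods. Against a fixed 82.7% with a two-sided limit, the error is 2.2-5.2% at the planned control rate and rises if the true control rate is higher.

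These figures assume 65 evaluable per arm, a 10-point absolute margin, one binary fusion result per participant and, except where stated, a 92.7% control rate. They do not show that a single-arm rule will be used; the surrounding text suggests otherwise. The sentence should still be corrected before analysis, because the primary conclusion rests on it.

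**What to change.** Replace the criterion with wording such as: rhBMP-2 is non-inferior if the lower confidence limit for the difference in the proportion of participants fused at 52 weeks (rhBMP-2 minus auto-iliac) lies above −10 percentage points.

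State the level and make it agree with the Sample size section, in one of two ways:
- Keep one-sided alpha 0.05 and use a one-sided 95% limit, which is the lower end of a two-sided 90% interval.
- Keep a two-sided 95% interval, restate alpha as one-sided 0.025, and restate the power. With equal true rates of 92.7% and 65 per arm, SE = √(2 × 0.927 × 0.073 / 65) = 0.0456 and 0.10 / 0.0456 = 2.19. Approximate power is then Φ(2.19 − 1.96) = 59%, against Φ(2.19 − 1.645) = 71% at one-sided 0.05.

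A score-type interval, such as Newcombe or Miettinen-Nurminen, is preferable. With rates near 93% and about 65 per arm, the Wald interval for the difference has size 3.3% against 2.5%, or 6.0% against 5%. This is a preference and could sit in the analysis plan.

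The cost is one sentence in the protocol, repeated in the analysis plan, with no extra data. Whether 154 participants are enough is a separate question that the rewording does not settle.

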**Methods:**

This trial is designed as a prospective, assessor-blinded, open-label, multicenter, randomized controlled study. Participants will be recruited from six tertiary teaching hospitals. All randomized participants will be undergoing one- or two-level TLIF with rhBMP-2 (77 participants) as the active experimental group or with an auto-iliac bone graft (77 participants) as the control group. The primary interbody fusion rate outcome will be evaluated using computed tomography (CT) 12 months after surgery. The secondary outcomes will be as follows: clinical outcomes (visual analog scale score, EuroQol-5-dimensions-5-level score, Oswestry Disability Index score, and some surgery-related variables) and adverse effects (radiculitis, heterotrophic ossification, endplate resorption, and osteolysis). Radiological outcomes will be evaluated using simple radiography or CT. All outcomes will be measured, collected, and evaluated before surgery and at 12, 24, and 52 weeks postoperatively.

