## Background

After the discovery of bone morphogenetic proteins by Marshall Urist in 1965 [1], the frequency of osteoinductive growth factor use in spinal surgery has significantly increased [2–5]. The use of recombinant human bone morphogenetic protein-2 (rhBMP-2) during lumbar fusion surgery as an alternative to autogenous bone graft can minimize complications, such as pain at the donor site, and it has been confirmed that it has the same effect as autologous long bone during spinal fusion [6, 7]. When rhBMP-2 was used in anterior lumbar interbody fusion (ALIF) and lateral lumbar interbody fusion (LLIF), high fusion rates were observed, respectively (94.5% and 92%) [8, 9]. Furthermore, the union rate of the transforaminal lumbar interbody fusion (TLIF) treated with rhBMP-2 was 96.6%, which was higher than that of the non-rhBMP-2 group (92.5%) [10, 11]. Therefore, rhBMP-2 may be a good substitute for bone fusion, which could be used to reduce iliac bone graft donor site morbidity [6]. Despite its high osteoinductivity, rhBMP-2 is difficult to apply clinically because it is extracted from mammals and expensive. However, *Escherichia coli*-derived rhBMP-2 shows a better extraction rate than that of mammals, and high osteogenic activity and cost-effectiveness have been reported [12, 13].

There is still no clear evidence on the clinical and radiographic efficacy and safety of *Escherichia coli*-derived rhBMP-2 on TLIF surgery. Therefore, a randomized controlled trial (RCT) is considered necessary. Specifically, we will compare the safety of using *E. coli*-derived rhBMP-2 with hydroxyapatite (HA) or autogenous iliac bones in patients in need of TLIF to complement the limitations of previous studies and confirm whether the *E. coli*-derived rhBMP-2 with HA bone union rate is non-inferior to that of autogenous iliac bone, as well as its clinical efficacy and safety.

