## Discussion

This study is designed to confirm the effectiveness and safety of *E. coli*-derived rhBMP-2 in one- or two-level TLIF. To analyze the efficacy of *E. coli*-derived rhBMP-2, the primary outcome, the 12-month interbody fusion rate on CT after surgery, will be compared to that of auto-iliac bone graft. We will also analyze clinical outcomes, such as ODI, EQ-5D-5L value, and VAS scores, radiographic outcomes, and complications.

Several studies have been conducted on the efficacy of rhBMP-2 in lumbar fusion surgery, and the fusion rate has been found to be equal to or higher than that of auto-iliac bone graft [6, 15, 16]. In addition, the use of rhBMP-2 has the advantage in that no morbidity occurs unlike when auto-iliac bone graft is harvested [17]. Therefore, rhBMP-2 has emerged as a good substitute for auto-iliac bone graft in spinal fusion surgeries. However, the use of rhBMP-2 in fusion surgery has side effects such as heterotrophic ossification, radiculitis, and end plate changes [14, 18–20]. In spite of the dosage-dependent side effects, rhBMP-2 has been widely utilized off-label without a defined dose. In the published literature, doses varied considerably from 40 mg in the AMPLIFY study to less than 1-mg per level, with a mean dose/level of 4 mg [15]. Fortunately, earlier research failed to detect a connection between rhBMP-2 dose and fusion rate [15]. In a retrospective case series, Lytle et al. reported that the use of 1 to 2 mg/level rhBMP-2 improved the fusion rate, although greater doses had no effect [21]. In the other known investigations, rhBMP-2 doses reported in prior research did not increase fusion rates [15]. Due to a lack of evidence for dosages smaller than 1.05 mg/level, we are not able to make definitive conclusions other than that there is no increased benefit for fusion by increasing the rhBMP-2 dose higher than 1.05 mg/level, which is the smallest commercially available dose. In addition, although minimal-dose studies for posterolateral fusion have been conducted, studies on TLIF are limited [22]. To confirm this, we will conduct a study using a low dose (0.5–1 mg per segment) of *E. coli*-derived rhBMP-2 to confirm the safety threshold of *E. coli*-derived rhBMP-2 and its efficacy.

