This study will be the first of its kind to analyze the effectiveness and safety of *E. coli*-derived rhBMP-2 with HA in one- to two-segment TLIF surgery. This study is designed to evaluate the non-inferior results between *E. coli*-derived rhBMP-2 with HA and auto-iliac bone graft using an appropriate sample size, blinded analyses, and prospective registration to reduce bias. This trial result will provide high-level evidence of the efficacy, safety, and standard indicators for the use of *E. coli*-derived rhBMP-2 in TLIF surgery.

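### The protocol sets out to confirm safety, but its only stated analysis of categorical side effects is a chi-square test of difference, and a non-significant result from it cannot confirm safety

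*Protocol article*

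**What the plan says.** **Aim.** The Discussion opens with "This study is designed to confirm the effectiveness and safety of" *E. coli*-derived rhBMP-2 in TLIF, and closes with "This trial result will provide high-level evidence of the efficacy, safety, and standard indicators for the use of" the product. The Background uses both registers. It says "Specifically, we will compare the safety of using" the two graft materials, then in the same sentence uses the verb confirm for non-inferior union together with clinical efficacy and safety. The Abstract and the section Trial design and participants speak only of evaluating safety.

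**Harms.** The Abstract's Methods paragraph lists among the secondary outcomes "adverse effects (radiculitis, heterotrophic ossification, endplate resorption, and osteolysis". The Discussion itself names heterotopic bone, radiculitis and endplate changes as known side effects of rhBMP-2.

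**Analysis.** Under Statistical analysis, "side effects between the two groups will be analyzed used by the chi-square test for categorical variables", with a t test for continuous ones. The significance rule is "Statistical significance will be defined as a two-sided *p* value < 0.05", with an exception only for the non-inferiority test. On the analysis set: "The mITT strategy will be the principle analysis for secondary outcomes".

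**Contrast with fusion.** The same section judges fusion by a confidence limit against a 10% margin. The Sample size section rests on the fusion rate alone. No expected harm rate, tolerable excess risk, confidence bound or power is given for any adverse effect.

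**The concern.** The stated aim and the stated test do not match. A chi-square test has no difference as its null hypothesis. Rejecting that hypothesis shows a harm (or a benefit). Not rejecting it shows only that the data did not settle the matter, and in a small trial that is the likely outcome for uncommon events even when the true excess is large. A claim that a treatment is safe, or no worse, needs a statement of how large an excess the data exclude. The protocol applies that logic to fusion and not to side effects.

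At stake is the published safety conclusion. With 77 or fewer participants per arm, a report of no significant difference in radiculitis or osteolysis could stand beside an interval that still allows a large excess of a harm the protocol attributes to the product. The primary fusion result is unaffected.

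**Working it through.** **Inputs from the article.** 154 participants, 1:1, so 77 per arm. Dropout of 15% at 12 months gives 77 × 0.85 = 65.45, taken as 65 per arm. The test is chi-square at two-sided 0.05. The figure of 154 belongs to fusion and is taken as given here. The article has no safety power or precision figure to reproduce.

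**Assumed.** Control-arm event rates, because the article gives none. The range shown is 2% to 15%.

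**Step 1: power to detect a raised harm rate.** For control rate p0, rhBMP-2 rate p1, n per arm and mean rate p̄:

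power ≈ Φ[(p1 − p0 − 1.96·s0)/s1], where s0 = √(2p̄(1 − p̄)/n) and s1 = √((p0(1 − p0) + p1(1 − p1))/n).

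At n = 77:
- 5% v 10%: s0 = 0.0424, s1 = 0.0423; (0.05 − 0.0832)/0.0423 = −0.79; power 22%.
- 5% v 15%: s0 = 0.0483, s1 = 0.0477; (0.10 − 0.0948)/0.0477 = 0.11; power 54%.
- 10% v 30%: s0 = 0.0645, s1 = 0.0624; (0.20 − 0.1264)/0.0624 = 1.18; power 88%.

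Exact enumeration of both binomial distributions, with the uncorrected chi-square rejecting above 3.84, agrees within about 2 points. The exact values are:

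| Control v rhBMP-2 | Ratio | 77 per arm | 65 per arm |
|---|---|---|---|
| 2% v 4% | 2 | 10% | 8% |
| 5% v 10% | 2 | 22% | 19% |
| 10% v 20% | 2 | 42% | 35% |
| 15% v 30% | 2 | 62% | 54% |
| 2% v 6% | 3 | 23% | 19% |
| 5% v 15% | 3 | 57% | 49% |
| 8% v 24% | 3 | 80% | 72% |
| 10% v 30% | 3 | 89% | 83% |

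**Step 2: where power falls below 50%.** Solving for the control rate at which power is one half gives, for a doubling, about 12% (77 per arm) and 14% (65 per arm). For a tripling it gives about 4% to 4.5% (77 per arm) and 5% (65 per arm). From a 5% control rate, 80% power needs an rhBMP-2 rate of about 19% (77 per arm) or 21% (65 per arm).

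**Step 3: what a non-significant result can conceal.** Take 11/77 v 4/77 events. The difference is 0.1429 − 0.0519 = 0.0909, chi-square 3.62, p = 0.057. The Wilson limits are 0.0817 to 0.2380 and 0.0204 to 0.1261. The Newcombe limits are:
- lower: 0.0909 − √(0.0612² + 0.0741²) = −0.005
- upper: 0.0909 + √(0.0951² + 0.0316²) = 0.191

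So a non-significant result goes with an interval of −0.5 to 19.1 points. For 8/77 v 4/77, an observed doubling, p = 0.23 and the interval is −3.8 to 14.5 points. For 12/77 v 4/77, an observed tripling, p = 0.035, which is significant.

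**Step 4: what this sample can support instead.** With equal true rates the approximate 95% half-width is 1.96·√(2p(1 − p)/77): 6.9 points at 5% and 9.5 points at 10%. Excluding a given excess δ with 80% power at one-sided 0.025 needs 2p(1 − p)(1.96 + 0.84)²/δ² per arm. For δ = 10 points that is 75 (5% rate) or 142 (10% rate). For δ = 5 points it is 299 or 566. These margins are illustrations, not figures from the article.

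**The case against.** A reader might infer that the protocol will treat p > 0.05 as proof of safety. It does not say so. The Statistical analysis section names a test, and the Safety reporting section says only that adverse events will be evaluated. No decision rule for safety is written, right or wrong. This part of the objection stands, and the point is therefore limited to the mismatch between aim and test.

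A reader might also infer that a doubled or tripled harm rate would usually go undetected whatever the baseline. That is too strong. A tripling from 8% or 10% would be detected about 72% to 89% of the time, a doubling from 15% more often than not, and an observed 12/77 v 4/77 reaches significance. The 11/77 v 4/77 example lies just short of the threshold and shows only how wide the interval is.

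Three further arguments have weight. The confirmatory wording is mainly in the Discussion, and softer verbs appear elsewhere. That lowers the gravity, but the Background uses the confirmatory verb too, so the article is inconsistent about its own aim. Next, intervals could be added in an analysis plan that is not shown, and a margin or power for each harm is not routine in a trial sized on efficacy. That is fair, and neither is asked for. But the aim and the test are both stated in the article, and an unseen plan would not remove their conflict. Last, 65 per arm is not the right number for every harm, since Table 2 records adverse events from the operation onward. That is why both sizes are shown.

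**Conclusion.** The point holds in this limited form: a difference test at two-sided 0.05, with no bound on excess risk and in a trial sized on fusion, cannot deliver the confirmation of safety that the article announces. The fault is the mismatch between a stated aim and a stated test, not a stated wrong decision rule.

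Its size rests on assumed control rates. For harms with a control rate below about 12% to 14%, a true doubling would more often than not be non-significant. For a true tripling this holds only below about 5%. For commoner harms the test has reasonable power against a tripling. The change should be made before the results are reported. It does not touch the primary analysis.

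**What to change.** 1. **Statistical analysis.** For each named adverse effect, report the between-arm risk difference with a two-sided 95% confidence interval (Newcombe). Keep the chi-square p value as supplementary at most.
2. **Same section.** State that p > 0.05 will not be taken as evidence of safety, and that any safety conclusion will quote the upper confidence limit, meaning the largest excess risk not ruled out.
3. **Background and Discussion.** Replace the wording on confirming safety, and on high-level evidence of safety, with estimating and comparing adverse-effect rates. This also removes the inconsistency with the Abstract and with Trial design and participants.

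No safety margin is proposed. The calculation above shows that excluding a 5-point excess would need several hundred participants per arm.

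The cost is a few sentences and one interval per adverse effect from data already planned, with no added patients or visits. The downside is a more modest safety claim.
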